#### Organization and functioning of the Movi-Kids programme

The Movi-Kids programme has been coordinated by two physical activity sciences graduates, and implemented by monitors with technical qualifications in physical activity and sports, physical education teachers or physical activity sciences graduates. The monitors were trained over two days, to standardize the actions of the activities programme.

#### Evaluation and follow-up

A telephone number, an email address and the blog (http://movi3kids.blogspot.com.es/) were available for parents and teachers over the two years. In addition, two meetings were conducted with monitors, at baseline and three months later. In each session, the monitors signed the list of participants to confirm who had attended the programme, and each month they gave a list of absentees to the programme’s coordinators by phone and email. When a child missed a programme’s sessions too often, the team called the family to find out the reasons. Finally, a quarterly visit to the centres was made to assess programme performance and conduct satisfaction surveys among the children. To encourage adherence to the Movi-Kids programme, children attending a minimum of 80 % of the trimester sessions were given positively reinforcement and received small gifts depicting the logo with the mascot of the programme.

#### Intervention with parents and teachers

Before the beginning of the programme, researchers, teachers and parents were asked to decide on the best way to implement modifications in the playground, and to discuss strategies to encourage family support of Movi-Kids. During the programme, several actions were taken to engage teachers and parents of the intervention group in promoting healthy lifestyles in children, as described.

### Statistical analysis

The sample size was estimated to be able to show differences between the control group and the intervention group of 2 % (alpha error, 0.05; statistical power, 0.80) in mean body fat at the end of the first year. The estimated sample size was 140 children per group; this figure was multiplied by an inflation factor for cluster-randomized trials [51], which was estimated at 1.1264 using measurements from previous studies in body mass index [52]. To examine subgroup differences (e.g., sex, age, ADHD or socio-economic status) under the same conditions, and estimating a 15 % dropout rate, the minimal sample size was estimated at 1600 children (800 per group).

The statistical analysis will be carried out in two phases. In the first, we will verify that the randomization was effective in creating two comparable groups, examining the differences between the control and intervention groups in mean body fat and academic achievement. After that, we will identify outliers and extreme values, and their trustworthiness. Finally, we will check the adjustment of the variables to the normal distribution by using the Kolmogorov–Smirnov test and graphical procedures (normal probability plot).

In the second phase, we will assess the change between the intermediate and final evaluation variables in the first and second years of the study. Mixed regression models [53] will be estimated using each outcome variable as a dependent variable at the end of the first and second years of the study. The different models will be adjusted for baseline values, age and school (cluster), and the interventions will be treated as fixed affects (1 = intervention group, 0 = control group).

The results will be expressed as absolute differences in change in variables between the baseline and the final measurements (confidence interval of 95 %). When the dependent variable is the prevalence of overweight or obesity, the odds ratio will be calculated, together with a 95 % confidence interval.

Because of the different patterns of weight and height, triceps skinfold thickness and body fat, the models will be separately implemented for boys and girls. A separate analysis will also be conducted for ADHD (with or without), socio-economic status, origin (native or foreign), area (urban or rural), and state-funded or private school.

Analyses will be carried out taking into account the CONSORT norms for the publication of the cluster design studies [54], with an intention-to-treat perspective, with children maintained in the group to which they were originally assigned, regardless of the number of sessions they attended.

Results will be considered statistically significant at *P* < 0.05, and the analysis will be performed using the 9.1 version of the SAS statistical package [55]. Mixed generalized lineal models will be used, PROC GENMOD for dichotomous variables, and PROC MIXED for continuous variables.

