## Abstract

**Background:**

The prevention of obesity and improvement of academic achievement in children are concerns of industrialized societies. Obesity has been associated with psychological disorders, including attention deficit hyperactivity disorder, whose prevalence has been estimated at 6.8 % in Spanish children and adolescents. It is known that physical activity is positively related to academic achievement and negatively related to the risk of obesity in children. However, studies to test the effectiveness of physical activity interventions in improving academic achievement in preschool children are scarce and have some weaknesses that threaten their validity. Moreover, very few studies have examined their effectiveness in improving symptoms of attention deficit hyperactivity disorder. This paper outlines a two-year multidimensional preschool intervention (Movi-Kids) aimed at preventing obesity and improving academic achievement in children with or without attention deficit hyperactivity disorder.

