The latest Cochrane review [23] highlights that there is consistent evidence regarding the effectiveness of interventions for preventing obesity in children aged 6 to 12 years. However, studies that address the effectiveness of such interventions in children younger than 6 years are scarce [23]. Only one study analyzed a healthy lifestyle promotional intervention (Ballabeina) in predominantly migrant preschool children, with successful effectiveness in reducing adiposity and improving fitness [24].

According to the Diagnostic and Statistical Manual of Mental Disorders, fifth edition (DSM-5) [25], attention deficit hyperactivity disorder (ADHD) is characterized by a persistent and impairing pattern of inattention, hyperactivity or impulsivity. A consistent body of evidence confirms that ADHD is often associated with other psychiatric conditions, such as specific learning disorders, mood and anxiety disorders, and sleep disturbances [26]. The aetiology of ADHD is complex and multidimensional, and combines both genetic and environmental factors. However, early diagnosis and appropriate treatment can positively influence its evolution [26–28]. In terms of prevalence, ADHD is one of the most common neurodevelopmental disorders in early childhood, affecting from 4.9 to 8.8 % of children and adolescents in Spain [29].

Interest has grown in the comorbidity between ADHD and other psychiatric and medical conditions. Clinical and epidemiological studies have consistently associated ADHD with overweight and obesity [30, 31]. Three mechanisms have been proposed to explain this relationship: (1) it has been suggested that two obesity-related factors, binge eating and excessive daytime sleepiness, might occur in children with ADHD, (2) obesity and ADHD share genetic and neurobiological abnormalities, such as dysfunctions in brain reward pathways, and (3) impulsivity and inattention are associated with irregular and dysregulated eating patterns, which contribute to weight gain [31].

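### The sample-size statement extends the 80% power condition to the ADHD subgroup, which at the article's own prevalence would have about 46 children per arm against the 140 to 158 required

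*Protocol article*

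**What the plan says.** In the Protocol article, Statistical analysis, the base calculation concerns the first-year assessment and targets "differences between the control group and the intervention group of 2 % (alpha error, 0.05; statistical power, 0.80) in mean body fat". The result is reported as "The estimated sample size was 140 children per group", multiplied by a cluster inflation factor, "which was estimated at 1.1264 using measurements from previous studies in body mass index". The total is then justified by "To examine subgroup differences (e.g., sex, age, ADHD or socio-economic status) under the same conditions, and estimating a 15 % dropout rate", which gives 1600 children, 800 per group.

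The same section plans separate analyses of children with and without ADHD. It does not call them exploratory and gives no ADHD-specific number.

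Prevalence is given twice. The Abstract refers to ADHD as a disorder "whose prevalence has been estimated at 6.8 % in Spanish children and adolescents". The Background section describes it as "affecting from 4.9 to 8.8 % of children and adolescents in Spain". Under Study design and participants, every child in the two school grades was invited, so the sample is not enriched for ADHD.

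**The concern.** The only conditions the paragraph sets are the difference, the alpha and the power. Its same-conditions phrase therefore most naturally carries all three into each named subgroup. A sample a little over four times the single-comparison requirement can do that for halves or quarters of the children. It cannot do so for a subgroup of roughly one child in fifteen.

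ADHD is not a side issue here. Benefit in children with or without the disorder is part of the stated aim, and the Background stresses how little evidence exists on exercise in such children. A reader who takes the sizing paragraph at face value would expect the ADHD result to be about as informative as the main comparison.

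**Working it through.** **Inputs.** From Statistical analysis: 2% difference (read as 2 percentage points), alpha 0.05 (two-sided assumed, as sidedness is not stated), power 0.80, 140 per group, factor 1.1264, dropout 15%, 800 per group. From the Abstract and Background: ADHD prevalence 6.8%, range 4.9 to 8.8%. Applying that prevalence to this sample is an assumption.

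**1. The plan's own figures.**
- The SD is not given. Solving for it: 2 / [(1.96 + 0.8416) × √(2/140)] = 5.97, a standardised difference of 0.335. Power depends only on this standardised value, which 140 per group at 80% power fixes.
- 140 × 1.1264 = 157.7 per group. Dividing by 0.85 gives 185.5 per group, or 371 in total for one comparison.
- Four such strata need 1484 children and five need 1855. The number of strata is not stated, so 1600 is neither reproduced nor shown to be wrong. It corresponds to 800 / 185.5 = 4.3 strata.

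**2. Where the claim works.** After dropout there are 800 × 0.85 = 680 per arm. With the 1.1264 factor, power for 2 points is 98% in half of the sample and 83% in a quarter. In a fifth (136 per arm) it is 74% with the factor and 79% without.

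**3. ADHD.** Number per arm = 680 × 0.068 = 46.2. Power = Φ(0.335 × √(n/2) − 1.96), with n divided by 1.1264 when the factor is applied.

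| Prevalence | n per arm | Power without factor | Power with factor |
|---|---|---|---|
| 4.9% | 33 | 28% | 25% |
| 6.8% | 46 | 36% | 33% |
| 8.8% | 60 | 45% | 41% |

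The most favourable two-sided case, 8.8% with no dropout (70 per arm), gives 51% without the factor and 46% with it.

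**4. Detectable difference at 80% power, 46.2 per arm.** Without the factor: 2 × √(140/46.24) = 3.48 points. With it: 2 × √(157.7/46.24) = 3.69 points.

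**5. What the stated condition would require.**
- ADHD share: 140/680 = 20.6% to 157.7/680 = 23.2%.
- Total at 6.8%: 2 × 140 / (0.85 × 0.068) = 4,844 without the factor, or 2 × 157.7 / (0.85 × 0.068) = 5,457 with it.

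**6. Allowing for baseline adjustment.** If 140 rests on a raw SD, adjustment at correlation r cuts the requirement by the factor 1 − r². Setting 140 × (1 − r²) = 46.24 gives r = 0.82. Starting from 157.7 gives r = 0.84.

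**7. If the phrase means a difference between subgroups.** For a 2-point interaction of arm with ADHD status, the standard error is 5.97 × √(2/46.24 + 2/633.76) = 1.29. Power is then 34% without the factor and 31% with it.

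**The case against.** The strongest objection is that 33 to 36% is not shown to be the power of the analysis that will be run. The models adjust for baseline values, and the calculation above does not. If the 140 was derived from a raw SD, power with 46 per arm would be about 46% at a correlation of 0.5, 62% at 0.7 and 77% at 0.8. If the 140 already allows for adjustment, there is no further gain. The article does not say which. This stands as a limit on the power figure, but it does not rescue the claim: the sizing paragraph states no correlation, and one above about 0.8 would be needed.

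Other objections narrow the point:
- The full 1.1264 factor is probably too large for this subgroup. About 92 children over 21 schools is about 4.4 per school, far fewer than in the whole sample, so the result without the factor is the more plausible end of each range.
- The prevalence covers children and adolescents, whereas this trial assesses ADHD risk with a rating scale at ages 4 to 7 and makes prevalence a secondary objective. The share could differ, but it would have to reach 21 to 23%.
- Results will be reported with 95% confidence intervals, so imprecision in a small stratum would be visible. That a null ADHD result would be mistaken for evidence of no effect is a risk, not a certainty.

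A reader might also infer that 1600 is an arithmetic error or that the main comparison is underpowered. The documents support neither. No sum is shown to be wrong, and the total is ample for the whole sample and for large subgroups.

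**Conclusion.** The point holds as a planning claim that the article's own figures do not support for ADHD. The expected 46 children per arm (33 to 60 over the quoted prevalence range) are under a third of the 140 to 158 required. On the unadjusted sizing basis this gives about 33 to 36% power for 2 points (25 to 45% over the range) and a detectable difference of about 3.5 to 3.7 points.

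This rests on a two-sided test, equal ADHD shares in the arms, the quoted prevalence applying to this sample, and the same-conditions phrase meaning the same difference, alpha and power. The shortfall in numbers is firm under those assumptions; the exact power is conditional on the unknown gain from baseline adjustment. The 80% claim is sound for subgroups of about a quarter of the sample or larger, and falls slightly short for five socio-economic categories even if they are of equal size. The correction should be made, but the main comparison is unaffected.

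**What to change.** Reword the sample-size paragraph:
- Limit the 80% power statement to subgroups of about a quarter of the sample or larger, such as sex and age.
- Remove ADHD from it. Remove socio-economic status too, unless its five categories are merged.
- State the expected ADHD number per arm (about 46, range 33 to 60), with its approximate power and detectable difference. Give the assumptions behind them: prevalence, dropout, cluster factor, and whether baseline adjustment is counted and at what correlation.
- Label the separate ADHD analysis exploratory.

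Keep the planned analysis with and without ADHD, because it answers the stated aim directly. An interaction between arm and baseline ADHD Rating Scale-IV score may be added as a supplement, with the informant and the score named in advance. It should not replace the split: it estimates something different, assumes a form for the effect modification, and does not by itself report the effect in children with ADHD.

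The cost is a few sentences and a less favourable stated power. No extra children or measurements are needed.

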## Methods/Design

### Study design and participants

A crossover randomized cluster trial was carried out, involving 21 schools located in as many municipalities in the provinces of Cuenca and Ciudad Real, in the Castilla-La Mancha region of Spain. All of them were state-funded schools except for two, which were private. In municipalities with more than one school, only one was selected for the study, to avoid contamination of the intervention. At first, 22 schools were invited, and only one of them refused to participate in the study, arguing that the study could mean excessive administrative overheads for the teachers. After the approval of school councils, the schools were randomly allocated using the statistical package StatsDirect to either the intervention or the control group; finally, the whole sample of schools was divided into three subgroups of randomization as follows: (i) nine public schools from Cuenca, (ii) ten public schools from Ciudad Real, and (iii) two private schools, one in the capital of each province (Fig. 1). All children belonging to the third grade of preschool and first grade of primary school (aged 4 to 7 years) were invited to participate.

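### The models omit the three randomization strata, so intervals and tests are conservative if province or school type predicts outcome; the amount is small on one reading of the article's own clustering figure and otherwise unknown

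*Protocol article*

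**What the plan says.** On allocation, the section on study design and participants states that "the whole sample of schools was divided into three subgroups of randomization as follows": "nine public schools from Cuenca, (ii) ten public schools from Ciudad Real, and (iii) two private schools", the last two being one in each provincial capital. The total is 21 schools.

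On analysis, the Statistical analysis section states: "Mixed regression models [53] will be estimated using each outcome variable as a dependent variable at the end of the first and second years". On covariates it states: "The different models will be adjusted for baseline values, age and school (cluster", and it adds the intervention as a fixed 1/0 term. Province, school type and stratum are not in that list. School type returns only among the separate analyses ("area (urban or rural), and state-funded or private school"). Province is not used in the analysis at all. The trial is powered for a difference of "2 % (alpha error, 0.05; statistical power, 0.80) in mean body fat at the end of the first year", which is a comparison between schools before any of them crosses over.

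**The concern.** When allocation is restricted within strata, stratum differences are largely removed from the contrast between arms. If the model has no stratum term, those differences still count as school-to-school variation and enter the standard error. The interval then describes a less balanced trial than the one that was run. With 21 schools, the between-school variance can carry much of the standard error, so this affects every outcome analysed between schools.

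What is at stake is efficiency in the reported result: a real effect could miss significance, or be reported less precisely than the design supports. False positive findings are not at stake.

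**Working it through.** **1. The plan's own figure.** The article gives "The estimated sample size was 140 children per group" and no standard deviation (SD). With two-sided alpha 0.05 (sidedness assumed) and power 0.80, n = 2(1.960 + 0.842)²SD²/2², so n = 140 needs SD = 2√(140/2)/2.802 = 5.97. The figure is therefore plausible but cannot be reproduced independently. Next, 140 × 1.1264 = 157.7, and 157.7/0.85 gives 186 per group; 800/186 = 4.3, and no multiplier is stated. None of this depends on the stratification.

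**2. Clustering implied by 1.1264.** ICC = 0.1264/(m − 1), with m children per school.
- m = 1600/21 = 76.2 gives 0.0017; m = 80 gives 0.0016.
- The article does not state the m behind the factor. It applies the factor to 140 per group. If m was 280/21 = 13.3 to 315/21 = 15.0 (an assumption), the ICC is 0.1264/12.3 = 0.010 to 0.1264/14.0 = 0.009.

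**3. Interval width without versus with stratum terms.** Let R be the share of between-school variance, after baseline adjustment, that the strata explain. School-level residual degrees of freedom are 21 − 2 = 19 without the strata and 21 − 4 = 17 with them (t = 2.093 and 2.110). Then

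ratio = √{[1 + (m − 1)ICC] / [1 + (m − 1)ICC(1 − R)]} × 2.093/2.110.

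Example at the article's factor with R = 0.5: √(1.1264/1.0632) × 0.992 = 1.029 × 0.992 = 1.02.

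| ICC (m about 76) | R = 0 | R = 0.25 | R = 0.5 | R = 1 |
|---|---|---|---|---|
| 0.0017 (factor 1.1264 at this m) | 0.99 | 1.01 | 1.02 | 1.05 |
| 0.01 (factor derived at about 14 per school) | 0.99 | 1.05 | 1.12 | 1.31 |
| 0.02 (assumed) | 0.99 | 1.08 | 1.19 | 1.57 |
| 0.05 (assumed) | 0.99 | 1.11 | 1.28 | 2.16 |

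The R = 1 column is a bound, not an expectation.

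**4. Simulation check.** School means were simulated for 21 schools in strata of 9, 10 and 2, with near-equal allocation within each stratum, 76 children per school, fixed stratum effects, no treatment effect and 20,000 trials per setting.
- ICC 0.0016: type I error without stratum terms was 4.7% (R = 0.25) and 4.5% (R = 0.5); width ratios were 1.01 and 1.02.
- ICC 0.02: type I error was 3.6% and 1.9%; width ratios were 1.08 and 1.21.
- With stratum terms, type I error in these settings was 4.9 to 5.1%.
- The SD of the treatment estimate at ICC 0.02 and R = 0.25 was 0.0739 without and 0.0736 with stratum terms.

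**5. Sensitivity to how the strata act.** If stratum effects are drawn at random, less of the nominal stratum variance appears between schools: 1 − (9² + 10² + 2²)/21² = 1 − 185/441 = 0.58 of it on average. Simulated this way at 65 children per school, the excess width is about 4% and 10 to 11% at ICC 0.02 (nominal R of 0.25 and 0.5), and about 8% and 20% at ICC 0.10. This is why the range for the assumed ICCs starts at 4%.

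**The case against.** **The crossover cancels stable stratum differences.** It would, if both years were analysed jointly with each school as its own control. The Statistical analysis section describes no such model. It takes the outcome at the end of the first and second years with a 1/0 intervention term and bases the sample size on the end of year one. It does not say whether school is fixed or random. In a single-year comparison, however, school has to be random, because fixed school effects would absorb the intervention. The objection stands only for a joint within-school analysis.

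**The covariate list may be condensed.** The article names other potential confounders that the model sentence also omits. Even so, the sentence reads as a specific list, and the randomization strata are part of the design, so this does not remove the point.

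**Baseline adjustment already does much of the work.** This is fair. Only stratum differences that remain after adjustment for each child's baseline count, and R may be small.

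**The private stratum has two schools.** This is also fair. It yields at most one between-arm contrast and adds little information.

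A reader might infer more than the article supports:
- *That the precision gained by stratifying is lost.* It is not. The estimate varies almost equally with and without stratum terms; only the credit for this in the reported interval is forgone.
- *That the intervals are certainly too wide.* This depends on R, which is not given. At R = 0 the planned interval is about 1% narrower.
- *That aptitude scores suffer most.* The article gives no clustering or stratum figure for them. It is only possible that the body mass index factor understates their clustering.

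**Conclusion.** The point holds in conditional form. The randomization used three strata, the stated models leave them out, and the between-school comparison at the end of a year is conservative to the extent that the strata predict outcome beyond baseline. The effect estimate is not biased and type I error is not inflated.

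The size cannot be read from the article. If 1.1264 applies at 76 to 80 children per school, the excess width is about 0 to 2% for R up to 0.5 and at most about 5%. If the factor was derived at about 14 children per school, it is about 5 to 12% for R of 0.25 to 0.5. Under assumed ICCs of 0.02 or more, which may apply to academic achievement, it is roughly 4 to 20% or more.

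These figures assume near-equal allocation within strata (the text gives no per-arm counts), equal school sizes, a continuous outcome and school as a random effect.

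**What to change.** Add the three-level randomization stratum (public Cuenca, public Ciudad Real, private) as a fixed effect in the primary and secondary models of the full sample, or state why it is left out. State also that school is a random effect in the single-year comparisons.

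In the separate analyses by school type, only province remains as a stratum term, and only among the state-funded schools. The two private schools lie one in each province, so no such term can be fitted there.

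The cost is one model term and two between-school degrees of freedom (17 instead of 19; t 2.110 instead of 2.093), or about 1% in interval width if the strata prove uninformative. Neither the design nor the sample size changes.
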